### Sample size and power calculation

Using the sample size tables published by Obuchowski *et al* for ‘Receiver Operating Characteristic Studies’,^35^ the study has been powered to detect small differences in the AUC (area under the receiver operating curve) of 0.05, with power of 80% and type 1 error rate of 5% between reader and AI algorithm performance. Assuming that the dataset will be representative of clinical practice with at least 20% abnormal cases, our sample size would need to be at least 112 examinations for at least 10 readers, per body part.

In order to ensure better representation of different abnormal findings, we have increased the number of examinations to 125 per body part, with approximately one-third of the cases being abnormal (ie, between 44 and 46 abnormal cases per body part, see online supplemental tables 1–3).

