### Objectives

In this study, the aim is to evaluate whether using a commercially available AI tool certified for paediatric use could help HCPs make better decisions about patient care.

Primary objective:

Determine differences in diagnostic accuracy rates of HCPs for paediatric fracture detection, before and after using the AI tool.

Secondary objectives:

Determine whether differences in accuracy rates or effect of adding AI varies according to job role and experience.Determine whether user confidence in fracture diagnosis changes when using the AI tool.Determine whether management plans are altered following the use of the AI tool.

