### Statistical methods/data analysis plan

The STARD-AI (Standards for Reporting of Diagnostic Accuracy - Artificial Intelligence) and CLAIM (Checklist for AI in Medical Imaging) guidelines will be adhered to in the reporting of this study.^33 34^ Diagnostic accuracy of the readers (with and without AI assistance) for each body part will be derived (ie, sensitivity, specificity, positive predictive value and negative predictive value). A true positive result will be counted if a mark made by a reader at the site of a suspected fracture falls within the area of the predefined ‘ground truth bounding box’ area set by the reference radiologists. If the mark made by a reader falls outside a bounding box, it will be counted as a false positive. Where a bounding box was set by the ground truth, but no mark made on the image then a false negative result will be assigned to the reader.

Estimates of these accuracy statistics will be derived through multilevel logistic regression models, with the reader included as a random-intercept. From these models, we will report 95% CIs, and p values (significance level set at 5%). Independent variables will be added, including the reader’s job role and experience, to assess their relationship with diagnostic accuracy. We will additionally present these same statistics to the reader, as derived through the random effects of the models, to explore the relationship between sensitivity and specificity. Intraobserver variability for the diagnostic accuracy of fracture detection before and after the use of AI assistance will also be evaluated, with subanalysis conducted to account for different reader medical specialty subgroups.

We will assess for differences in confidence scores for correctly identified images between HCPs with and without AI guidance, and also whether there were significant differences between readers across specialties and experience levels. We will also evaluate how an indeterminate AI reading affects reader decisions.

Changes in clinical management will be compared using descriptive statistics (ie, frequency and percentages) to determine, for example, how many children would be discharged with a missed fracture, or unnecessary second opinions/additional imaging sought for cases with and without AI assistance. This could provide information to help estimate potential future benefit and cost savings to the NHS at a future clinical implementation stage, where appropriate.

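### The stated 80% power is for an AUC difference between readers and the AI algorithm, which matches neither the planned comparison (readers without v with AI) nor the planned measures

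*Protocol article*

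**What the plan says.** The section *Sample size and power calculation* relies on published sample-size tables for ROC studies. On the measure, it says "the study has been powered to detect small differences in the AUC (area under the receiver operating curve) of 0.05". The same sentence goes on to name the power, the error rate and the contrast: "with power of 80% and type 1 error rate of 5% between reader and AI algorithm performance". It assumes a dataset "representative of clinical practice with at least 20% abnormal cases" and concludes that "our sample size would need to be at least 112 examinations for at least 10 readers, per body part". The planned numbers were then raised to 125 examinations per body part, 44 to 46 of them abnormal.

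The primary objective is: "Determine differences in diagnostic accuracy rates of HCPs for paediatric fracture detection, before and after using the AI tool". Under *Study design*, each reader is their own control over two reading stages, the first without and the second with AI.

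Under *Statistical methods/data analysis plan*, the accuracy measures are "sensitivity, specificity, positive predictive value and negative predictive value", estimated by multilevel logistic regression with a random intercept for reader. AUC and ROC are mentioned only in the sample size section. The 5-point confidence score is analysed as confidence for correctly identified images, not as a rating from which an ROC curve is built.

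**The concern.** A power statement is useful only if it refers to a test that will be done. This one departs from the plan in two ways:

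- **Contrast.** It names readers against the algorithm. The objective and design compare readers without AI with the same readers using AI.
- **Measure.** It is set on AUC. The planned outputs are proportions at each reader's own operating point. A difference of 0.05 in AUC does not translate into a fixed difference in sensitivity or specificity, and the variances differ. Sensitivity in particular rests only on the abnormal examinations.

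At stake is how the results are read. A null or imprecise result for sensitivity, overall or in one body part, would be judged against a claim of 80% power that was not calculated for it.

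**Working it through.** **1. Plan against power statement**

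| | Sample size section | Objective, design, analysis |
|---|---|---|
| Contrast | reader v AI algorithm | same readers, without v with AI |
| Measure | AUC, difference 0.05 | sensitivity, specificity, PPV, NPV |
| Readers | at least 10 | at least 40 |
| Examinations per body part | at least 112, at least 20% abnormal | 125, with 44 to 46 abnormal |

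The counts agree with each other: 4 × 125 = 500; 181 abnormal lies between 4 × 44 = 176 and 4 × 46 = 184; 181/500 = 36.2%; 500 − 181 = 319 normal.

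**2. Can 112 examinations and 10 readers be reproduced?**

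The protocol gives no baseline AUC, reader spread or correlations, so these are assumed. For a multireader multicase (MRMC) comparison of two reading conditions in the same J readers, power comes from a non-central F with 1 and J − 1 degrees of freedom and

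λ = J d² / (2 [σb²(1 − rb) + σc²{(1 − r1) + (J − 1)(r2 − r3)}]).

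Here σb is the between-reader SD (range/4), rb the correlation of reader effects between conditions, and σc² the case variance of one AUC. The error correlations are r1 (same reader, different conditions), r2 (different readers, same condition) and r3 (different readers, different conditions).

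- Inputs from the protocol: d = 0.05, J = 10, 112 × 0.20 = 22.4 abnormal, 4 normal per abnormal.
- Assumed: AUC 0.90, reader range 0.05, r1 = 0.47, r2 = r3 = 0.30, rb = 0.8, two-sided 5%.
- Binormal variance: A = 1.414 × Φ⁻¹(0.90) = 1.812, so A² = 3.284. σc² = 0.0099 × exp(−A²/2) × [(5A² + 8) + (A² + 8)/4] / 22.4 = 0.0099 × 0.1936 × 27.24 / 22.4 = 0.00233.
- Bracket: (0.0125)² × 0.2 + 0.00233 × 0.53 = 0.00003 + 0.00124 = 0.00127.
- λ = 10 × 0.0025 / (2 × 0.00127) = 9.87, and power = 79.8%.

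So 112 fits a two-condition AUC comparison in the same readers. It is not confirmed. Over assumed AUC 0.75 to 0.95, reader range 0.01 to 0.10 and several sets of correlations, the number required for 80% power runs from 51 to 585.

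**3. Does 80% carry over to the planned measures?**

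The same formula applies with binomial variance p(1 − p)/n. Take a 5-point gain in sensitivity from an assumed 70%, with 40 readers, reader range 0.1, rb = 0.8, r1 = 0.5 and r2 = 0.4. Only r3 is varied. J d² = 40 × 0.0025 = 0.1, and the reader term is (0.025)² × 0.2 = 0.000125.

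*Per body part, 45 abnormal, variance 0.21/45 = 0.00467:*
- r3 = 0.4: λ = 0.1 / (2 × [0.000125 + 0.00467 × 0.5]) = 20.3, power about 99%.
- r3 = 0.2: λ = 0.1 / (2 × [0.000125 + 0.00467 × 8.3]) = 1.29, power about 20%.

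*Pooled, 181 abnormal, variance 0.21/181 = 0.00116:*
- r3 = 0.4: λ = 0.1 / (2 × [0.000125 + 0.00116 × 0.5]) = 70.9, power over 99%.
- r3 = 0.2: λ = 0.1 / (2 × [0.000125 + 0.00116 × 8.3]) = 5.13, power about 60%.

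Wider illustrative ranges for a 5-point gain (sensitivity baseline 70% to 85%, specificity baseline 85% to 90%, reader range 0.1 to 0.2) are:

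| | Per body part | Pooled |
|---|---|---|
| Sensitivity | about 20% to over 99% (45 abnormal) | about 57% to over 99% (181 abnormal) |
| Specificity | about 50% to over 99% (about 80 normal) | about 93% to over 99% (319 normal) |

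**The case against.** The strongest reply is that the contrast is only a slip of wording. The figures fit a comparison of two conditions in the same readers, which is the actual design, and the tables cited are for ROC studies. The check in step 2 supports this, and I accept it as the likely explanation. It removes the mismatch of contrast once the sentence is corrected. It does not remove the mismatch of measure, because no AUC is planned. An unseen analysis plan could add an AUC, but it could not make the sentences in this protocol agree with each other.

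The second reply is that the plan exceeds its own minimum: at least 40 readers against 10, 125 examinations against 112, and about 36% abnormal against 20%. That is also right. A reader might infer that the study is underpowered, and the protocol does not support that inference. Power for the planned comparison may well be adequate, above all when body parts are pooled.

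A reader might go further and say that the 5% level belongs to no planned test, or count every measure in every body part as a confirmatory test and conclude that 5% is not held. The protocol does not support this either. The analysis section sets its own nominal 5% level for the planned p values. *Study design* lists body part among the subgroup analyses. At a fixed prevalence, PPV and NPV follow from sensitivity and specificity, so the measures are not separate independent tests. The choice of a primary measure and a testing order is commonly left to an analysis plan, which is not shown here.

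**Conclusion.** The point holds as an inconsistency between sections. The 80% power is stated for a measure that the plan does not analyse and, as worded, for a contrast that it does not test. That conclusion comes from the text alone and needs no assumptions.

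The size of the consequence cannot be fixed from the protocol. The stated sample size is plausible for AUC without v with AI (79.8% under the assumed inputs). For a 5-point gain in sensitivity per body part, the same method gives anything from about 20% to over 99%. The decisive unknown is how strongly different readers' errors agree within a condition compared with across conditions (r2 − r3), for which the protocol gives no figure. The spread shows that the 80% cannot be transferred. It is not evidence of low power. Nor would it help to quote power for readers against the stand-alone algorithm, since no such test is planned.

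**What to change.** In *Sample size and power calculation*, replace the words naming reader and algorithm with: between readers without and with AI assistance. Then do one of the following.

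(a) Restate the calculation as the detectable difference in sensitivity and in specificity at 80% power for 40 readers, 181 abnormal and 319 normal examinations, and also per body part. State the assumed baseline rates, reader variance and correlations, and show a range for each. Take these from sources other than this study's own results.

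(b) Keep AUC as the powered measure and add an MRMC analysis of AUC without v with AI to the analysis section. The fracture mark and the 5-point confidence score can be combined into an ordered rating, from certain of no fracture to certain of fracture, so no new data are needed. State the baseline AUC, reader range and correlations behind the 112 examinations and 10 readers.

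The cost is rewording and a recalculation, with no extra readers or cases. Under (a) the per-body-part figure may look less favourable than the present statement.

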### Patient and public involvement

In designing this research protocol and in the application for the funding, the NIHR GOSH Biomedical Research Centre Patient and Public Advisory Groups for research were consulted which included ‘The Young Persons Advisory Group (YPAG)’ (comprising 24 young people, aged 11–21 years) and ‘The Parent and Carer Advisory Group (PCAG)’ (comprising 5 parent representatives).^36^ Many of the children were familiar with the concept of AI,^37^ and of these, four YPAG and three PCAG members volunteered to form the ‘FRACTURE Patient and Public Involvement & Engagement (PPIE) Steering Committee’ for this project and related works.^38^ Their input has confirmed to us that patients prefer to see how doctors can be helped (rather than replaced) by AI, and therefore, this study aims to understand if AI can enhance current clinical practices and the impact this could have on patient care.

### Ethics and dissemination

#### Human research ethics committee approval

This study was granted approval by NHS Health Research Authority (HRA) and Health and Care Research Wales (HCRW) (REC Reference: 22/PR/0334). IRAS Project ID is 274 278. Informed consent was not required for the use of fully anonymised, retrospective imaging data for this study. Written consent will be received by all readers within this study prior to the interpretation exercises.

### Intended publications and research dissemination

Datasets generated and/or analysed during the current study are not publicly available due to data confidentiality agreements with data custodians. Results generated by the research will be made publicly available at the summary level. Manuscripts addressing the study aims will be published in peer-reviewed journals and will also be presented at relevant national and international conferences. Findings will also be disseminated via social media and online blogs.

Study outcomes will be disseminated to all relevant clinical and non-clinical stakeholders which include our FRACTURE PPIE Steering Group, the wider Great Ormond Street Hospital YPAG and PCAG members, members of the ESPR, ESSR, BSPR, BSSR, SoR, RCEM, APEM, BSCOS, members of the NIHR Imaging Science Working Group and also the Clinical AI interest group of the Alan Turing Institute. The findings and awareness raised by the study and its dissemination will help inform future AI evaluation for paediatric healthcare, policy decisions and raise awareness of AI training needs for various multidisciplinary subspecialties and HCPs who may encounter such tools as part of their role.
